## Abstract

**Background:**

Elderly population in low- and middle-income countries is rapidly growing, which indicates an increase in the number of dependent people needing long-term care. Caring for the elderly is difficult and stressful and threatens physical and mental health of informal caregivers. We aim to design a web-based support group and assess its effectiveness on depression, anxiety, and stress among elderly informal caregivers.

**Methods:**

This is a protocol for a two-arm randomized controlled trial. A total of 160 informal elderly caregivers will be recruited from the southern area of Tehran. Eligible participants will be randomly allocated to two intervention and control groups. The inclusion criteria include not receiving salary for caring, having primary responsibility for care, having smartphone/tablet/computer, being able to use the contents and web applications, having at least one month of experience in caring for the elderly, and having access to the Internet at least once weekly. The intervention will be implemented by giving an account access to the designed website. Depression, anxiety, and stress will be assessed using the DASS21 questionnaire at baseline, and at the end of third and sixth months.

**Discussion:**

Our findings can pave the way for improving the mental health of informal caregivers of the elderly through provision of web-based supportive services. This study stands as an opportunity to address the needs of caregivers and help them support each other in a novel way.

**Trial registration:**

Iran Randomized Clinical Trial Center IRCT20201012048999N1. Registered on 25 December 2020 (current status: ongoing).

The World Health Organization Trial Registration Data Set is in Additional file 1

**Protocol version:**

Second version 2021-05-27

**Supplementary Information:**

The online version contains supplementary material available at 10.1186/s13063-022-06351-4.

## Administrative information

Note: The numbers in curly brackets in this protocol refer to SPIRIT checklist item numbers. The order of the items has been modified to group similar items (see http://www.equator-network.org/reporting-guidelines/spirit-2727-statement-defining-standard-protocol-items-for-clinical-trials/).'

## Introduction

### Background and rationale {6a}

Generally, the world’s population is aging. The number of people aged 60 and over, which was about 900 million in 2015, is projected to reach two billion by 2050 [1]. This growth rate varies among countries. It began in high-income countries and is currently increasing in low- and middle-income countries [2]. In Iran, the elderly population is more than seven million people [3], representing 9.2% of the total population in 2016. It is predicted that by 2050, the Iranian elderly population will grow by 10.5% in 2025 and 21.7% in 2050 [4].

Aging of societies will eventually result in an increase in the number of dependent individuals in need of long-term care [5]. Many elderly people lose the ability to live independently due to limited mobility and/or other physical and mental health problems, which makes their needs more pressing for specific kinds of long-term health care and social support. It is estimated that 349 million people worldwide are care-dependent, of which 29% are 60 years old or over. A large number of elderly receive informal care from their family members and/or friends [6].

In recent years, the burden of care is increasing in Iran due to a reduction in household size. Moreover, due to strong emotional ties between family members, and cultural context, families do not place the elderly in long-term care centers [7]. Caring for others is recognized as an important social role that can improve caregiver’s self-esteem and overall well-being; however, it can be a source of stress, tension, unhealthy behaviors, and social restrictions [8, 9]. It may also decrease quality of life of caregiver and increase mortality [8]. Those who care for dependent people find their lives totally affected in a way that they cannot do their own works as well as their family responsibilities [10]. Informal caregiver may not only show care-related stress but also revive conflicts, anger, grief, low self-esteem, frustration, physical burden, time constraints, role pressures, and financial challenges. A long-term family caregiver is sometimes called “a second victim” or “a potential patient” [11].

Caregivers for disabled individuals are at risk of developing depression. In a study conducted in China, it was reported that the prevalence of depression among caregivers was 37.7% [9]. Depression adversely influences behavior, cognition, and emotions and significantly reduces the quality of care. Moreover, depression may lead to physical pain and even raise the tendency to commit suicide [11].

Anxiety is another important negative emotional implication of care, for which the rate depends on the type of care. The anxiety rate ranges from 21.4% among caregivers of stroke patients to 43.6% in caregivers of dementia patients [10].

Informal caregivers rely on a wide range of internal and external resources for health information, support, and counseling, including health-care professionals, printed materials, and web-based resources, to do their job properly. Among support group interventions, the ones that provide interactions with peers and professionals, e.g., web-based support groups, are of particular importance [12]. Caregivers can use support group websites to search for information, receive emotional support, use the experience and advice from other caregivers, and learn how to better self-care [12, 13]. Studies have also highlighted the positive effects of web-based support groups, including reducing loneliness, gaining identity, giving a sense of social inclusion, belonging, comfort and acceptance, hope, and a safe environment [12–14]. These web-based support groups are deemed a feasible and cost-effective intervention to support caregivers. Instant and easy access to these groups allows members to avoid the need to leave the care recipient, thus removing a main barrier to participating, i.e., spending time to attend face-to-face meetings and the need to find an alternative caregiver [13]. In addition, in-person support groups may be difficult to access due to high health care workload and/or geographical restrictions [14]; multiple daily activities such as housekeeping, employment, and caring for other family members; and fear of being labeled [15].

In Iran, a number of support groups and self-help interventions have been implemented and have resulted in fruitful results. However, no study is available to assess the effect of web-based support groups among elderly caregivers. This protocol aims at proposing the backbone for a study with the purpose of assessing the effect of a web-based support group entitled “Mehrpishegan” on depression, anxiety, and stress in informal primary caregivers of elderly in Tehran.

## Objectives {7}

This is the protocol for our study, which aims to assess the effect of Mehrpishegan web-based support groups on depression, anxiety, and stress in elderly informal primary caregivers. The hypothesis of this study is that there is a difference in the status of depression, anxiety, and stress among the participant caregivers before and after implementing the intervention.

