## Trial design {8}

This is a parallel group, two-armed, superiority, single-blinded, randomized trial. The number of participants in intervention and control groups will be equal. Randomization will be performed using block randomization with a 1:1 allocation. The control group will not be exposed to the intervention during the study.

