### Outcomes {12}

This study has three primary outcome variables (depression, anxiety, and stress) that are going to be measured by the DASS-21 scale three times during the study: before (T0), by the end of the first 3 months of the intervention (T1), and by the end of the second 3 months (T2) after the intervention. The effect of the web-based support group on depression, anxiety, and stress in the intervention and control groups will be assessed and compared before and after the intervention. The difference in the mean scores of the outcomes will be assessed.

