### Sample size {14}

The study population consists of informal primary caregivers of the elderly in the South Tehran, who have the willingness to participate. The sample size has been calculated using PASS 15.0.5 software. Based on literature [18] and using Cohen’s formula (expecting the average effect size) with a coefficient = 0.5 φ [19], for both of the intervention and control groups (63 people), taking into account the power of 80. The effect size is 0.50 and the significance level (alpha) will be 5%, the probability of drop-out and withdrawal of the study is 20%, equivalent to 80 people in each group, and the total will be 160 people.

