### Recruitment {15}

We will seek help from the South Tehran Health Center, hospitals, and other organizations in the area to cooperate to promote adequate enrolment. We will explain the aims and process of the study to their staff. We will ask them to advertise our study on virtual social networks and invite caregivers to participate in it. We will continue advertising until we reach the expected sample size. Furthermore, we will review the health records of elderly people in order to identify dependent elderly people and their caregivers, which were compiled in the South Tehran Health Center. Informal caregivers will be invited to participate according to inclusion criteria using telephone invitations. The purpose of the study, possible pros and cons of participation in the study, assurances of confidentiality, and the process of conducting the study will be explained to the caregivers. Also, the Mehrpishgan website will be introduced. If the individuals are interested in participating in the study and are eligible, they will receive a username and password and will be asked to complete the online consent form and the baseline measurement on the website. Before the commencement of the intervention, participants who will be in mild and moderate categories (based on DASS-21 scores) will be randomly assigned to one of the intervention or control groups.

Afterwards, participants in the intervention group will be asked to establish their activities in the web-support group for 6 months. At the end of the third month and sixth month, T1 and T2 assessments will be conducted in both intervention and control groups.

The control group will not be exposed to any intervention during the study. However, after completing the T2, they can use facilities of the website (Fig. 1).

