## Statistical methods

### Statistical methods for primary and secondary outcomes {20a}

All eligible participants in the study who will be randomly assigned to the groups will be considered the Full Analysis Set (FAS) that will make up the intent to treat analysis (ITT) population. The per-protocol population is a subset of the ITT population that has no violations of the study protocol (type of intervention and timing specified). Information on all quantitative data will be reported as mean (standard deviation) or median interquartile range (IQR), while qualitative data will be reported as frequency and percentage. We will compare the two groups to measure the effectiveness of the intervention and changes in the outcomes (depression, anxiety, and stress) over time using the repeated measures ANOVA test. The SPSS and STATA will be used for analysis of data.

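### The stated hypothesis is a before-after difference among participants, which contradicts the two-arm superiority design, the two-group sample size and the planned group comparison

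*Protocol article*

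**What the plan says.** - Objectives {7} first gives the aim, to assess the effect of the support group. It then gives the hypothesis that "there is a difference in the status of depression, anxiety, and stress among the participant caregivers before and after implementing the intervention". No other section states a hypothesis.
- Outcomes {12} names both arms but keeps the before-after wording: the effect "in the intervention and control groups will be assessed and compared before and after the intervention". It adds that a difference in mean scores will be assessed, without saying between what.
- Trial design {8}: "This is a parallel group, two-armed, superiority, single-blinded, randomized trial", and "Randomization will be performed using block randomization with a 1:1 allocation".
- Sample size {14} uses an effect size of 0.50, alpha 5% and power 80%, giving 63 people per group, raised to 80 per group (160 in total) for 20% drop-out.
- Statistical methods {20a}: "We will compare the two groups to measure the effectiveness of the intervention and changes in the outcomes" over time, by repeated measures ANOVA. The term that decides effectiveness is not named.
- Recruitment {15}: "participants who will be in mild and moderate categories (based on DASS-21 scores) will be randomly assigned". Blinding {17a} repeats this rule. DASS-21 is also the outcome measure.

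**The concern.** A hypothesis about change from before to after the intervention is a different claim from a difference between randomised arms. Read as written, {7} would be supported if the participants' scores changed over six months, even if controls changed by the same amount. Randomisation protects the between-arm contrast only. It gives no protection against causes of change that act on both arms alike.

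One such cause is plausible here, because people are admitted on the basis of a single baseline reading of the outcome scale. If the mild-to-moderate band lies above the average of the caregivers screened, later scores will tend to drift back in both arms without any treatment. At stake is whether a significant change over time could be presented as confirming the trial hypothesis.

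**Working it through.** **1. Which contrast does the sample size serve?** Inputs from {14}: d = 0.50, alpha 5%, power 80%. Two-sided, two-sample normal formula:

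n per group = 2(z₀.₉₇₅ + z₀.₈₀)² / d² = 2(1.960 + 0.842)² / 0.25 = 62.8, so 63.

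This reproduces the stated 63. Drop-out: 63 / 0.80 = 78.75, so 79. The t-test version gives 64 per group, and 64 / 0.80 = 80, the stated figure. A one-sided test would need 2(1.645 + 0.842)² / 0.25 = 49.5, so 50, which does not match. The trial is thus sized for a two-sided difference between two arms, which {7} does not state.

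**2. The sections side by side.**

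| Section | Contrast described |
|---|---|
| Objectives {7} | before versus after, no control arm |
| Outcomes {12} | both arms named, compared before and after |
| Trial design {8} | two-arm superiority |
| Sample size {14} | two-sample difference, d = 0.50 |
| Statistical methods {20a} | two groups compared; ANOVA with group, time and group-by-time terms |

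Of the three ANOVA terms, time is the one that matches {7}. The term that matches {8} and {14} is a group or group-by-time contrast.

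**3. How often would a before-after test succeed with no intervention effect?** The documents give no DASS-21 mean, SD or retest correlation, so what follows is assumed. Scores are normal with SD 1, and baseline is restricted to a band from a to b, in SD units from the source mean. The correlation r between baseline and follow-up is 0.5 to 0.9, and there are 63 people per arm.

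- Baseline mean in the band: m = [φ(a) − φ(b)] / [Φ(b) − Φ(a)].
- Expected change: −(1 − r)m.
- SD of change: √[(1 − r)²v + 1 − r²], where v is the baseline variance within the band.

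Example, band 0.5 to 1.5: m = (0.352 − 0.130) / 0.242 = 0.92 and v = 0.077. At r = 0.5 the change is −0.46 and its SD 0.877, so the expected paired t is −0.46 × √63 / 0.877 = −4.2. For r = 0.6, 0.7 and 0.8 the changes are −0.37, −0.28 and −0.18, with t of −3.6, −3.0 and −2.4.

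Share of simulated trials with p < 0.05 (4,000 per setting; r = 0.5, 0.7, 0.8 and 0.9; each range runs over r):

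| Band (SD from source mean) | Before-after, one arm | Before-after, both arms pooled | Between arms, on change |
|---|---|---|---|
| −0.5 to 0.5 | about 5% | about 5% | 4% to 5% |
| 0 to 1 | 14% to 52% | 22% to 83% | 4% to 6% |
| 0.5 to 1.5 | 38% to 98% | 66% to 100% | 5% |

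The lower rates belong to r = 0.9 and the higher to r = 0.5. The pooled column is the closer analogue of the ANOVA time effect, though it uses two visits and not three.

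**4. Where might the band lie?** The Background cites caregiver depression of 37.7% and anxiety of 21.4% to 43.6%. If those shares marked the boundary between normal and mild on a normal scale, the band would start 0.16 SD (43.6%), 0.31 SD (37.7%) or 0.79 SD (21.4%) above the mean. This is only a rough guide, since the instruments and populations may differ.

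**The case against.** The strongest reply is that {20a} ties effectiveness to a comparison of the two groups, {14} is sized for that comparison, {12} names both arms, and the first sentence of {7} speaks of the effect of the support group. No section plans a paired test within one arm. This stands. A reader might infer from {7} that no between-arm analysis is planned, or that success will be declared on a one-arm before-after test. The documents do not support either reading. They do not remove the contradiction, though: {20a} leaves open which ANOVA term decides, and {7} points to time. An article may leave the choice of term to an analysis plan, but a hypothesis stated for the wrong contrast is an error in the article itself.

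A second reply is that regression to the mean is not established. This also stands in part. The entry rule excludes severe as well as normal scorers, so the direction of drift depends on where the band sits, and a centred band gives no net drift. The documents do not say which of the three scales must be mild or moderate, and a scale on which a person was not selected need not regress by the amounts above. A reader might infer that a fall in both arms is certain, or that a before-after test would usually be significant. For the band 0 to 1 SD above the mean, the one-arm rate passes one half only at the lowest correlation tried. The contradiction in the text does not depend on these figures.

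**Conclusion.** The point holds as a wrongly stated hypothesis. {7}, echoed in {12}, describes change over time, while {8}, {14} and {20a} describe a difference between arms. Because {20a} does not say which term decides, a change common to both arms would literally confirm the hypothesis as written.

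How often that would happen without any intervention effect cannot be fixed from the documents. Under the stated assumptions the one-arm rate runs from about 5% (band centred on the source mean) to 98% (band 0.5 to 1.5 SD above it, correlation 0.5), while the between-arm rate stays at 4.3% to 5.7%. Natural course or secular change could have the same consequence, and neither is quantified here. The planned data can answer the right question, so this is a fault in the statement of the hypothesis and its link to the analysis, not in the design.

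**What to change.** - **{7} and {12}:** for each DASS-21 scale, state the hypothesis as a difference between arms in score at follow-up, adjusted for the baseline score already collected. Change from baseline compared between arms serves the same purpose.
- **{20a}:** state that effectiveness is judged on that between-arm contrast, and not on the time effect or on change within an arm. The contrast is the group term if baseline is a covariate, or group-by-time if baseline is one of the repeated measures.

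Within-arm changes may still be reported; whether to attach p-values to them is a matter of reporting preference.

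The cost is a small amendment to the objectives, outcomes and analysis text. It goes slightly beyond rewording, because {20a} changes too. The sample size, visits and data collection stay as they are. As recruitment has begun, the amendment should be dated before the outcome data are analysed.

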## Trial design {8}

This is a parallel group, two-armed, superiority, single-blinded, randomized trial. The number of participants in intervention and control groups will be equal. Randomization will be performed using block randomization with a 1:1 allocation. The control group will not be exposed to the intervention during the study.

## Methods: participants, interventions, and outcomes

### Study setting {9}

This study will be conducted in the South Tehran, which includes four urban and two rural areas. The healthcare services in the South Tehran are covered by the South Tehran Health Center. The population coverage of the whole area is more than three million people; of those, about 80,000 are over 60 years old [16]. We will be in contact with 15 local health centers and two hospitals from this area that provide health and medical care to the elderly in order to recruit the informal caregivers (Additional file 2).

### Eligibility criteria {10}

The inclusion criteria include not receiving salary for caring, having primary responsibility for care, having smartphone/tablet/computer, being able to use the contents and web applications, having at least 1 month of experience in caring for the elderly, and having access to the Internet at least once weekly. Any informal caregiver diagnosed with mental illness and undergone treatment, those participating in other support groups (virtual or non-virtual), or non-Iranian caregivers will be excluded.

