#### Criteria for discontinuing or modifying allocated interventions {11b}

Termination of care tasks (change of care status to non-primary caregiver, death or recovery of the elderly); the participant’s request; leaving the support group and not using the website; undergoing any kinds of medical treatments; emergence of an adverse issue during the study that seriously affects the individual’s mental health, such as divorce or death of close relatives; or any behavior that threatens or harms other participants will result in exclusion from the study or discontinuing the intervention.

To estimate the efficacy, all participants will be analyzed according to randomization assignment (ITT approach) as a full analysis set (FAS) population. In addition, per protocol (PP) approach will be done as well.

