#### Relevant concomitant care permitted or prohibited during the trial {11d}

Since the informal caregivers for elderly are not registered as caregivers in any health or social care system, they do not receive any special care services. As a result, participants will be able to obtain the same health and social services as the general public during the trial, but they will be excluded if they require mental health therapy.

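### The entry exclusion on mental illness and the in-trial exclusion on need for therapy test different states, so a caregiver can be randomised and then removed for a condition already present at entry

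*Protocol article*

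**What the plan says.** All places are in the protocol article.

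- Eligibility criteria {10}: the mental-health exclusion at entry is "Any informal caregiver diagnosed with mental illness and undergone treatment". Two conditions are joined by 'and'. Neither current nor past treatment is specified.
- Relevant concomitant care {11d}: participants may use ordinary health and social services, but "they will be excluded if they require mental health therapy". Need alone is the test.
- Criteria for discontinuing or modifying allocated interventions {11b}: the listed events include "undergoing any kinds of medical treatments", and they "will result in exclusion from the study or discontinuing the intervention". The text does not say which event leads to which consequence.
- The same section: "all participants will be analyzed according to randomization assignment (ITT approach) as a full analysis set (FAS) population". Statistical methods {20a} also defines the full analysis set as all eligible participants who were randomised.
- Recruitment {15} adds a second entry filter: "participants who will be in mild and moderate categories (based on DASS-21 scores) will be randomly assigned". Who will be blinded {17a} repeats it.

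**The concern.** An exclusion applied before allocation cannot bias the comparison between arms; the same exclusion applied afterwards can. Here the in-trial rule reaches people whom the entry rule lets through, so some removals that could have been screen failures become post-randomisation losses.

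Three features make these losses awkward.

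- **Related to outcome.** The trigger is mental-health state, and the three primary outcomes are depression, anxiety and stress.
- **Detected by unblinded people, with unequal contact.** Only the data analyst is blinded ({17a}). Allocation is revealed to the doctoral student ({16c}), who also recruits, collects data, implements the intervention and follows participants ({5d}). For the first three months the intervention arm has a weekly session with a psychologist, and the researchers join its group and forums ({11c}). Both arms get questionnaire reminders and contact if needed ({18b}), but no scheduled professional contact is described for controls.
- **At odds with the analysis commitment.** A participant excluded from the study and not followed can stay in the full analysis set only through imputed values ({20c} names simple linear regression). The outcome is then a model's guess for the very people whose course is least typical.

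**Working it through.** **1. The two rules side by side, for a caregiver's state at screening**

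| State at screening | Entry rule {10} | In-trial rule {11d} |
|---|---|---|
| Diagnosed, in treatment | Barred, on the natural reading | Not reached |
| Diagnosed, untreated, needs therapy | Admitted | Meets the ground for exclusion |
| Diagnosed, untreated, does not need therapy | Admitted | Not excluded |
| No diagnosis, needs therapy | Admitted | Meets the ground for exclusion |
| No diagnosis, already in counselling | Admitted | Meets it if being in therapy counts as requiring it; {11b} may also apply if counselling counts as medical treatment |

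The second, fourth and fifth rows are the gap.

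**2. Does the DASS-21 filter close it?** Caregivers scoring severe or very severe are not randomised, which removes many with the greatest need. But the scale scores symptoms. It does not ask about diagnosis, current therapy or need for therapy, and those who pass have been selected for having some symptoms. Participants also see their score at once ({18a}), which might prompt some to seek help. The gap is narrowed, not closed.

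**3. How a removal becomes bias.** Suppose fractions p_I and p_C of the two arms are removed and their outcomes would have been k SD worse than those of the rest of their arm. The mean of those retained then looks better than the full arm's mean by p × k in each arm. The comparison shifts by (p_I − p_C) × k. Equal detection (with equal k) cancels; unequal detection does not. If more cases are found in the intervention arm, the shift favours the intervention. The documents give none of these three quantities, so no number is attached.

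**4. Is it a power problem?** Inputs from Sample size {14}: d = 0.50, alpha 5% (two-sided assumed), power 80%, drop-out 20%.

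- Plan's own figure: n = 2 × (1.960 + 0.842)² / 0.50² = 62.8, so 63 per arm, as stated ("for both of the intervention and control groups (63 people), taking into account the power of 80"). The t-test version gives 63.8, so 64.
- Inflation: 63 / 0.80 = 78.75, so 79; 64 / 0.80 = 80. The stated 80 per arm is reproduced.
- Planned loss: 160 × 0.20 = 32.
- Assumed removals of 5% to 15%: 160 × 0.05 = 8 to 160 × 0.15 = 24.
- Power = Φ(0.50 × √(n/2) − 1.960), with n per arm:

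| Scenario | n per arm | Power |
|---|---|---|
| Removals fall within the 20% allowance | 80 × 0.80 = 64 | 80.7% |
| A further 5% on top | 64 × 0.95 = 60.8 | 78.7% |
| A further 10% on top | 64 × 0.90 = 57.6 | 76.5% |
| A further 15% on top | 64 × 0.85 = 54.4 | 74.1% |

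Over the assumed range the allowance covers the loss if other drop-out leaves room. Even if it does not, the cost in power is a few points.

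**The case against.** The strongest reply is that the two rules need not match. One is an eligibility criterion; the other governs care during the trial and must also cover need that first arises after allocation. A difference between them is not by itself an error. Moreover, {11d} sets no procedure or timing for finding such cases, and an untreated diagnosis does not by itself mean that therapy is required. All of this stands, and it limits how many removals can be traced to the entry wording. It does not remove the overlap: the in-trial rule as written also catches need that was there at screening.

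A second reply is that the bias comes from post-randomisation exclusion as such, so rewording the entry rule cannot cure it. This also stands in part, and is why the fix has two halves.

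A reader might infer more than the text supports:

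- *That the entry rule generally admits people already in therapy.* A diagnosed caregiver in treatment is most naturally covered by the exclusion; only someone treated without a diagnosis slips through.
- *That anyone ever treated is barred.* The rule requires a diagnosis as well. Barring previously treated caregivers is a legitimate choice of population, and a look-back window is a detail that an article may leave to the full protocol.
- *That the trial selects those most likely to need therapy.* The DASS-21 filter works against this by removing the severe categories.
- *That the caregiver prevalences in the Background (depression 37.7%, anxiety 21.4% to 43.6%) show how many would be affected.* They come from other caregiver populations and say nothing about treatment or need for it.

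**Conclusion.** The concern holds in a limited form. The entry rule ({10}), the discontinuation rule ({11b}) and the concomitant-care rule ({11d}) are not aligned. On a literal reading, a caregiver can be randomised and then excluded for a mental-health state present at entry. Such exclusions are related to the primary outcomes, are open to unequal detection, and conflict with the ITT/FAS statements in {11b} and {20a}.

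The size cannot be derived from the documents. The 8 to 24 of 160 rests wholly on an assumed 5% to 15%. Some exclusions under {11d} will reflect need that arose after randomisation, which no screening question could prevent. The stated sample size reproduces and is not in question. A claim that the trial loses its power this way is not supported; the issue is avoidable bias.

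**What to change.** 1. **Before allocation.** Reconcile {10}, {11b} and {11d} so that any mental-health state that leads to exclusion is checked at the existing telephone screening contact, before randomisation. Which states qualify, and how they are worded, is for the sponsor and its psychiatrist adviser to settle.
2. **After allocation.** State that a participant who starts or comes to need therapy has this recorded with its date, is still asked for T1 and T2, and stays in the ITT analysis in the allocated arm. In {11b}, separate stopping the intervention from leaving the study. Whether such a participant continues in the support group is a clinical decision on which this review takes no position.

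The cost is one or two extra screening questions, a few more screen failures, and two follow-up questionnaires for participants who would otherwise have been dropped. As recruitment is described as under way, the eligibility change would go through the amendment route in {25}.
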